**Figure 5. Procedure for recording MVIC data and induced supra-maximal contraction in the participant**

Once each participant reaches a plateau in torque output, a supramaximal electrical stimulus will be delivered to activate motor units that were not voluntarily recruited, thereby eliciting a stronger muscle contraction. This approach is commonly used to quantify deficits in quadriceps activation following ACLR, through measurement of the Central Activation Ratio (CAR) using the Superimposed Burst Technique (SIBT) ([91](#_ENREF_91)).

For this procedure, two square-shaped electrodes (each measuring 20 cm²) will be used for electrical stimulation. One electrode will be placed proximally on the lateral aspect of the quadriceps muscle, and the other distally on the medial aspect, secured firmly with elastic bandages.

To calculate CAR, the peak voluntary torque generated immediately before the electrical stimulus is divided by the peak torque produced in response to the stimulus (i.e., the superimposed burst torque) ([51](#_ENREF_51)) (Figure 5).

**tDCS Electrode Placement Procedure**

For the tDCS intervention, electrode pads will first be moistened with normal saline solution. The anodal electrode, embedded within the pad, will then be secured using Velcro straps over the M1 region. Electrode positioning will be determined using the international 10–20 EEG system ([42](#_ENREF_42)).

The vertex (Cz) is a key anatomical landmark in this system, located at the intersection of the line connecting the inion and nasion with the line connecting the preauricular points. The inion is the most prominent point on the occipital bone, while the nasion lies between the forehead and nose, at the junction of the nasal bones.

To locate the M1, a distance equivalent to 20% of the interaural distance is measured laterally from the vertex. This corresponds to the C3 or C4 positions in the EEG system. The anodal electrode will be placed over C3 or C4, contralateral to the dominant limb, while the return (cathodal) electrode will be positioned over the supraorbital region ([101](#_ENREF_101)). Electrode placement is illustrated in Figure 6.

[figure not shown]

**Figure 6. Electrode placement: anode over M1 and cathode over the supraorbital area**

**tDCS Stimulation Parameters and Sham Protocol**

In this study, the anodal and cathodal electrodes will measure 24 cm² and 35 cm², respectively. The stimulation duration will be 20 minutes, with a current intensity of 2 mA. This level of current has been shown to induce changes in cortical excitability that may persist for up to 1.5 hours following stimulation ([10](#_ENREF_10)). Additionally, this intensity is considered safe and well-tolerated by participants ([42](#_ENREF_42)).

The stimulation protocol involves a gradual ramp-up of current from 0.1 mA to 2 mA over 30 seconds at the beginning of the session, followed by a gradual ramp-down over 30 seconds at the end of the 20-minute stimulation period.

For the sham intervention, the current will similarly ramp up over 30 seconds and then immediately ramp down, mimicking the sensation of active stimulation. This standardized sham procedure minimizes the likelihood of participants distinguishing between real and placebo stimulation ([50](#_ENREF_50)). Previous studies have reported that participants typically experience a tingling sensation within 10 to 20 seconds of sham stimulation, similar to that of active tDCS ([102](#_ENREF_102)).

**Intervention Protocol**

In the intervention group, participants will receive ten sessions of motor cortex tDCS, administered four times per week. The control group will follow the same schedule, but with sham stimulation. This study will be conducted under a double-blind design, ensuring that both the assessor and participants remain unaware of whether the stimulation is active or sham.

Each physiotherapy session will last 60 minutes and include the following components:

Used to retrain quadriceps muscle activation and enhance strength. Two carbon rubber electrodes (4 × 6 cm), covered with moistened sponge pads, will be placed on the proximal and distal bulk of the quadriceps muscle—one on the vastus lateralis and the other on the vastus medialis. For the hamstring muscle, two similar electrodes will be placed on its proximal and distal bulk (Figure 7).

FES parameters will include trapezoidal pulse currents with 2-second ramp-up and ramp-down times, a pulse duration of 250 microseconds, a frequency of 50 Hz, and a stimulation-to-rest ratio of 1:2 (6 seconds contraction, 12 seconds rest). Stimulation will be applied for 20 minutes per session ([39](#_ENREF_39)), with a maximum intensity of 100 mA ([94](#_ENREF_94)). The physiotherapist will adjust the intensity in each session according to the participant’s tolerance to maximize motor unit recruitment. Participants will be instructed to perform voluntary muscle contractions during the stimulation phase ([103](#_ENREF_103)).

Applied for pain reduction. Two carbon rubber electrodes (4 × 6 cm), covered with moistened sponge pads, will be placed on either side of the knee (Figure 7). TENS will be delivered in conventional mode at a frequency of 100 Hz for 20 minutes per session ([39](#_ENREF_39)).

[figure not shown]

**Figure 7. Electrode placement for FES current application**

**10.8. Instruments Used in the Study**

1. Demographic Questionnaire – Used to collect background variables including age, height, weight, occupation, duration of condition, and the operated limb (Appendix 1).

2. Measuring Tape and Clinical Scale – For assessing participants’ height and weight.

3. Device used for electrical stimulation to induce SIBT

4. tDCS Device (Activedose) – Manufactured by ActivaTeK™ (Taiwan), used for transcranial direct current stimulation.

5. Dynamometer – For measuring maximal voluntary isometric contraction (MVIC) of the quadriceps muscle.

6. KOOS Questionnaire – Knee Injury and Osteoarthritis Outcome Score (Appendix 4).

7. IKDC Questionnaire – International Knee Documentation Committee form (Appendix 5).

8. ACL-RSI Questionnaire – Anterior Cruciate Ligament–Return to Sport after Injury scale (Appendix 6).

**12. Statistical Methods for Data Analysis**

Descriptive results will be presented using tables, charts, and measures of central tendency and dispersion. The normality of data distribution will be assessed using the Shapiro–Wilk test.

Given the crossover design of the study and the quantitative nature of the dependent variables, comparisons between the two interventions will include analysis of carry-over effects, sequence or period effects, and treatment effects. Depending on the distribution of the data, either the independent samples t-test or its non-parametric equivalent, the Mann–Whitney U test, will be used.

The significance level (Type I error) is set at 0.05; therefore, p-values less than 0.05 will be considered statistically significant. All statistical analyses will be performed using SPSS version 25, and graphical representations will be generated using Microsoft Excel 2018.

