7.3. Specific Analytical Objectives

1. To compare the effect of motor cortex a-tDCS with sham tDCS on quadriceps strength in individuals post-ACLR, relative to the control group, before and after stimulation.

2. To compare quadriceps muscle strength in ACLR individuals before and after motor cortex stimulation with tDCS.

3. To compare central activation ratio to quantify quadriceps activation failure before and after motor cortex stimulation with tDCS.

4. To assess the correlation between a-tDCS parameters and total KOOS scores and domain scores in the intervention and control groups before and after tDCS.

5. To assess the correlation between a-tDCS and IKDC questionnaire scores in the intervention and control groups before and after tDCS.

6. To assess the correlation between a-tDCS and ACL-RSI questionnaire scores in the intervention and control groups before and after tDCS.

7. To assess the correlation between a-tDCS and VAS-reported pain scores in the intervention and control groups before and after tDCS.

8. To compare KOOS questionnaire scores in the intervention and control groups before and after tDCS.

9. To compare IKDC questionnaire scores in the intervention and control groups before and after tDCS.

10. To compare ACL-RSI questionnaire scores in the intervention and control groups before and after tDCS.

11. To compare VAS pain scores in the intervention and control groups before and after tDCS.

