**Study Design, Randomization, and Blinding**

This study will follow a parallel-group design. After completion of the pilot phase and determination of the final sample size, eligible participants will be randomly assigned to one of two groups: (1) routine physiotherapy plus a-tDCS, or (2) routine physiotherapy plus sham tDCS (s-tDCS).

Randomization will be performed by an independent individual not involved in the study, using sealed, opaque envelopes containing each participant’s identification number and assigned group (active/sham). All assessments will be conducted by the principal investigator, while tDCS (active or sham) will be administered by a separate individual who is blinded to the study details.

To ensure double-blinding, participants will remain unaware of the nature of the intervention they receive, and the assessor will be blinded to group allocation. To achieve this, tDCS stimulation and baseline physiotherapy treatment, as well as pre- and post-intervention assessments, will be conducted independently by two separate individuals.

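### Section 12 plans carry-over and sequence/period analyses for a crossover, but the trial is parallel-group; these effects cannot be estimated and the quantity under test is left unclear

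*Protocol*

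**What the plan says.** Section 12 begins its inferential plan with "Given the crossover design of the study and the quantitative nature of the dependent variables". It then says that "comparisons between the two interventions will include analysis of carry-over effects, sequence or period effects, and treatment effects". The next sentence says that, depending on the distribution, "either the independent samples t-test or its non-parametric equivalent, the Mann–Whitney U test, will be used". Alpha is 0.05. The section does not name the quantity to which the tests apply.

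Under Study Design, Randomization, and Blinding the protocol says "This study will follow a parallel-group design" and that "eligible participants will be randomly assigned to one of two groups", physiotherapy plus active or plus sham stimulation. Under Intervention Protocol, the intervention group receives ten sessions, and "The control group will follow the same schedule, but with sham stimulation". The dynamometer section measures quadriceps strength before the first session and again after the ten sessions.

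Section 10.6 plans a pilot of 10 participants, from which the final sample size will be calculated.

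In Section 7.3, objective 4 is "To assess the correlation between a-tDCS parameters and total KOOS scores and domain scores". Objectives 5 to 7 ask for correlations of a-tDCS, without the word parameters, with IKDC, ACL-RSI and VAS. Objectives 8 to 11 compare KOOS, IKDC, ACL-RSI and VAS between groups.

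**The concern.** Two current sections describe incompatible designs, and one of them is the protocol's only analysis section. An analyst who follows Section 12 is told to look for effects that exist only when each participant receives both treatments in sequence.

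Two things are at stake. First, two-sample tests are used both in parallel trials (on post values or changes) and in crossovers (comparing sequence groups on period sums or differences). Coming straight after the crossover sentence, the named tests have no fixed target, so the choice could be made after the data are seen. Second, the final sample size is still to be calculated, and whoever does so from Section 12 could use a crossover formula.

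**Working it through.** The protocol gives no figure to reproduce on this point. The check sets the sections side by side, then asks what a crossover model could estimate from the data this trial collects.

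**1. What the methods describe**

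| Feature of a crossover | This trial |
|---|---|
| Each participant receives both treatments | No. One group each (Section 4; 10.7; Study Design, Randomization, and Blinding) |
| Two or more treatment periods | No. One block of ten sessions (Intervention Protocol) |
| Switch and washout | None described for this trial |
| Outcome after each period | One assessment before and one after (dynamometer section) |

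The crossovers and the washout mentioned in Section 6 belong to cited studies.

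**2. What can be estimated**

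Take a model with five fixed effects: intercept, sequence, period, treatment and carry-over.

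- Two-period crossover: rank 4 of 4 without carry-over; rank 4 of 5 with it, because carry-over is aliased with sequence.
- This trial, post values only: rank 2 of 5. Only an overall mean and a difference between arms can be estimated.
- This trial, pre and post values: rank 4 of 5. The carry-over column is entirely zero, because no treatment precedes another. The sequence term is just arm membership and the period term is just time. The treatment term is estimable, as the difference between arms in change.

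Carry-over is therefore empty, and sequence and period lose their crossover meaning. The treatment contrast survives.

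**3. Do the named tests work in a parallel trial?**

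Type I error was simulated at two-sided alpha 0.05 with a pre/post correlation of 0.7. The sidedness, the correlation and the sizes of 15 and 17 per arm are assumptions; 5 per arm is the pilot of 10 split equally.

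| n per arm | t-test, post | t-test, change | Mann–Whitney, post |
|---|---|---|---|
| 5 | 0.051 | 0.049 | 0.037 |
| 15 | 0.050 | 0.051 | 0.047 |
| 17 | 0.050 | 0.050 | 0.052 |

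The t-test holds its level. Mann–Whitney is somewhat conservative at 5 per arm and close to nominal otherwise.

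**4. Size of the sample-size risk**

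Let σ² be the common variance, r the within-person correlation and N the total number of participants. The variance of the estimated treatment effect is:

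- crossover: 2σ²(1 − r)/N
- parallel, post values: 4σ²/N
- parallel, change: 8σ²(1 − r)/N
- parallel, baseline-adjusted: 4σ²(1 − r²)/N

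For equal precision, the crossover N as a fraction of the parallel N is:

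- against post values: 2(1 − r)/4 = (1 − r)/2, which is 25% at r = 0.5 and 15% at r = 0.7
- against change: 2(1 − r)/[8(1 − r)] = 25% at any r
- against baseline adjustment: 2(1 − r)/[4(1 − r²)] = 1/[2(1 + r)], which is 1/3.0 = 33% at r = 0.5 and 1/3.4 = 29% at r = 0.7

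The protocol gives no correlation, so r = 0.5 and 0.7 are assumptions.

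**5. Objective 4**

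The protocol fixes stimulation at 2 mA, 20 minutes and ten sessions. Within the active arm these parameters have zero variance, so a correlation with them is undefined there.

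**The case against.** The strongest reply is that the crossover words are a drafting slip and that the operative sentence is the next one. It names two tests for independent groups, which fit the parallel design, and the simulation shows that they behave properly. This largely stands. A reader might infer from the crossover wording that no valid primary test is left, or that Section 12 yields no estimate of active against sham. The document does not support that: the treatment effect is estimable, and the named tests address it.

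A reader might also picture baseline and follow-up being treated as two periods, with a carry-over test on their sum and a fallback to the first period, which would compare baselines. Section 12 defines no such mapping, test or fallback, so that harm is not attributed to the plan.

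On the objectives, it is tempting to say that all of 4 to 7 correlate scores with a constant. Only objective 4 mentions parameters. Objectives 5 to 7 say a-tDCS and cover both groups; read as arm membership, that is a binary variable and the correlation can be computed. It merely duplicates the comparisons in objectives 9 to 11.

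A statistical analysis plan that is not shown might define the primary quantity, but it could not remove a contradiction inside the protocol. Nor does the reply settle which quantity the tests address.

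**Conclusion.** Section 12 is wrong as written and should be corrected before the final sample size is set and the data are analysed. Carry-over and sequence/period effects cannot be estimated in the crossover sense. This follows from the design and rests on no numerical assumption. The primary comparison is ambiguous, not absent.

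The sample-size consequence is conditional. If a crossover formula were used, the trial would have about 15% to 33% of the participants needed, depending on the parallel analysis it is set against and on r between 0.5 and 0.7, with equal variances and the same r between periods as between baseline and follow-up. Nothing in Section 10.6 says that such a formula will be used, and that section also lets the available pool and time determine the final number.

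The objective 4 defect is secondary, and the case for correcting Section 12 does not depend on it.

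**What to change.** - Replace the crossover sentence in Section 12 with a statement that this is a two-arm parallel-group trial, and delete the carry-over, sequence and period effects.
- State the primary analysis: the between-arm difference in post-intervention quadriceps MVIC, analysed as randomised and adjusted for baseline MVIC (ANCOVA), with its 95% CI.
- Keep the independent samples t-test and the Mann–Whitney test as the simple and non-parametric alternatives, applied to change from baseline.
- In Section 10.6, state that the final sample size will be calculated for the parallel design and this analysis.
- Reword or delete objective 4. Delete objectives 5 to 7 if they mean arm membership, since objectives 9 to 11 cover them, and align research questions 6 to 9.

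This changes protocol wording only. Baseline MVIC is already collected, so the correction needs no extra measurements. A parallel calculation may give a larger number than a crossover formula would, but that is what the design requires.

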**10.6. Sample Size Determination**

Due to the absence of prior studies using a similar methodology, the present study will be conducted as a pilot involving 10 participants. Based on the outcomes obtained from this initial sample, the final sample size will be calculated. Ultimately, the number of participants will be determined according to the available sample pool and the time constraints of the study.

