The average torque from the five MVIC attempts will be used to quantify quadriceps strength. This procedure will be conducted prior to the tDCS intervention to establish baseline strength values. The same protocol will be repeated following completion of ten tDCS sessions to assess post-intervention changes in muscle strength.

[figure not shown]
.
[figure not shown]

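### Section 12 names only unadjusted two-sample tests, picked by a normality pre-test, without saying whether they compare post values or changes; a baseline-adjusted model would use data already collected

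*Protocol*

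**What the plan says.** Section 12 of the protocol settles the between-group method in some detail. "The normality of data distribution will be assessed using the Shapiro–Wilk test", and then, "Depending on the distribution of the data", "either the independent samples t-test or its non-parametric equivalent, the Mann–Whitney U test, will be used". It also fixes the error rate: "The significance level (Type I error) is set at 0.05". It names no covariate and no baseline-adjusted model, and it does not identify the variable to be tested.

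Baseline data are nevertheless planned. On the mean torque of five maximal contractions (MVIC), the dynamometer section says: "This procedure will be conducted prior to the tDCS intervention to establish baseline strength values". The same protocol is "repeated following completion of ten tDCS sessions to assess post-intervention changes in muscle strength". Section 10.7 has the IKDC, ACL-RSI, KOOS and VAS completed before the intervention, and Section 7.3 compares these scores and the central activation ratio before and after. The first analytical objective in Section 7.3 concerns the effect of active against sham stimulation "on quadriceps strength in individuals post-ACLR, relative to the control group, before and after stimulation".

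On size, Section 10.6 says "the present study will be conducted as a pilot involving 10 participants". The final number is to be calculated from that pilot but ultimately depends on how many participants and how much time are available; no figure is given.

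**The concern.** Strength two months after reconstruction is likely to differ widely between athletes and to be correlated within an athlete. That is the setting in which adjusting for the baseline value brings the largest gain in precision. A two-sample test on post values leaves the gain unused. The randomisation section mentions no stratification by strength, so any chance difference in baseline strength between arms adds to the noise in that comparison.

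Leaving the analysed variable open is a second weakness. A test on post values and a test on changes can give different answers on the same data, and nothing in Section 12 stops the choice being made after the data are seen.

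Third, the Shapiro–Wilk result decides whether the trial reports a mean difference or a rank comparison. The quantity being estimated then depends on a pre-test that has little power in small samples.

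With the final size limited by availability, efficiency of analysis is one of the few levers left.

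**Working it through.** **Stated figures.** The protocol gives no effect size, SD, power, final sample size or baseline–post correlation, so there is no figure of its own to reproduce.

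**Inputs**
- Tests and selection rule: Section 12.
- Alpha 0.05: Section 12. Sidedness is not stated; two-sided is assumed.
- Correlation rho between baseline and post values: assumed 0.6, 0.8 and 0.9, with lower values where noted.
- 17 per arm: assumed. It is the size of the ACL-injury stimulation trial of 34 athletes in the literature review, not this trial's size.
- True difference 0.5 SD: assumed.
- 5 per arm: an equal split of the pilot of 10, also an assumption.

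**Variance of the treatment comparison**, relative to a test on post values, with equal SD before and after:
- post values: 1
- change: 2(1 − rho)
- ANCOVA: 1 − rho²
- ANCOVA relative to change: (1 − rho²) / [2(1 − rho)] = (1 + rho)/2

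| rho | post | change | ANCOVA | ANCOVA/change |
|---|---|---|---|---|
| 0.6 | 1 | 0.80 | 0.64 | 0.80 |
| 0.8 | 1 | 0.40 | 0.36 | 0.90 |
| 0.9 | 1 | 0.20 | 0.19 | 0.95 |

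Against post values, the patient-number equivalent is 1/0.64 = 1.6, 1/0.36 = 2.8 and 1/0.19 = 5.3. Against change scores, the saving is 20, 10 and 5%. Below rho = 0.5 a change score is worse than the post value alone: at rho = 0.3 its factor is 2 × 0.7 = 1.4.

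**Power, 17 per arm, 0.5 SD.** The noncentrality is (0.5/√factor) × √(17/2), with 32 degrees of freedom for the two t-tests and 31 for ANCOVA. For post values it is 0.5 × 2.915 = 1.46. For ANCOVA at rho = 0.8 it is (0.5/0.6) × 2.915 = 2.43.

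| rho | post | change | ANCOVA |
|---|---|---|---|
| 0.6 | 29% | 35% | 42% |
| 0.8 | 29% | 61% | 65% |
| 0.9 | 29% | 89% | 90% |

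The formula slightly flatters ANCOVA because it omits the cost of estimating the slope. Simulation that includes this cost (6,000 runs) gave change against ANCOVA of 35 v 41, 61 v 64 and 88 v 88%.

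**Very small samples.** At 5 per arm and 0.5 SD, simulated power for change against ANCOVA was 20 v 19% at rho 0.8 and 37 v 32% at rho 0.9. With a 0.8 SD effect (3,000 runs) it was 44 v 41% and 71 v 66%. The advantage over change scores is gone there.

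**Normality pre-test.** With normal data, type I error of the post-value comparison when Shapiro–Wilk chose the test was 0.044 to 0.058 (2,000 runs per setting), and power barely moved. Against a lognormal shape with sigma 0.5, Shapiro–Wilk rejected normality in about 10% of samples of 5, 25% of samples of 10 and 44% of samples of 17.

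**The case against.** A reader might infer that the plan ignores the baseline altogether. The documents do not establish that. The dynamometer section describes the repeat measurement as a way to assess changes, and Section 7.3 words its objectives as before and after. An independent-samples t-test on change scores is therefore a natural reading, and it uses the baseline. The multiples of 1.6, 2.8 and 5.3 apply only if post values are compared. On the change reading, the gain at 17 per arm is a few percentage points of power, and at about 5 per arm with high correlation there may be none.

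A reader might also infer that the Shapiro–Wilk step damages the error rate. The simulations with normal data show no material effect. What stands is narrower: a weak pre-test decides which quantity is reported.

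An unadjusted test in a randomised parallel trial is also valid. Chance imbalance is unbiased over randomisation and is already reflected in the standard error, so this is a matter of efficiency and prespecification.

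Finally, the choice of covariate and analysed variable could be left to a statistical analysis plan that is not shown. That would be decisive had Section 12 deferred the method. Instead it names the tests and the rule for choosing between them, so the point concerns what is fixed.

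The same paragraph has a larger fault: it introduces these tests on the premise of a crossover, with carry-over and period effects, whereas the randomisation section states parallel groups. The tests may be leftover crossover text. That strengthens the case for rewriting Section 12 and does not remove this point.

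**Conclusion.** The point holds as an efficiency and prespecification weakness that should be corrected. Section 12 fixes unadjusted tests, leaves the analysed variable open and lets a low-powered pre-test choose between them, while the baseline values needed for a better analysis are already to be collected.

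The size depends on the reading. The loss is substantial if post values are compared and correlation is high: 29% power against about 65% for ANCOVA at rho 0.8. It is modest if changes are compared: 61 against about 65% at the same rho. It may be nil at about 5 per arm with high correlation. The correlation, the 17 per arm and the 0.5 SD effect are all assumptions, because the protocol states none of them.

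**What to change.** In Section 12, for the parallel-group comparison, prespecify one primary analysis: a linear model of post-intervention MVIC on randomised arm and baseline MVIC, reporting the adjusted difference with its 95% confidence interval. Use the same form for the central activation ratio, KOOS, IKDC, ACL-RSI and VAS, each with its own baseline value.

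Replace the Shapiro–Wilk-driven choice of test with this model, plus a rank-based or permutation version as a sensitivity analysis. In the same edit, reconcile the crossover, carry-over and period wording with the parallel-group design stated under randomisation.

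The cost is a few lines of text. No new data are needed, and SPSS 25, already named in Section 12, fits the primary model. The statistical price is one degree of freedom, which matters slightly only at very small numbers.
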